#### **7.4.2.2 Randomized Sub-study (Central Laboratory)**

One sample for CKMB or Troponin I/T must be taken in the post-procedural hospitalization period. A second sample should be taken within 3 to 6 hours after the first post-procedure sample, but no later than 24 hours after the procedure.

One sample for Creatinine must be taken in the post-procedural hospitalization period.

### **7.4.3 Medications**

#### **7.4.3.1 SPIRIT WOMEN Single Arm Study**

It is recommended that patients enrolled in the SPIRIT WOMEN Single Arm Study should be maintained on 75 mg of clopidogrel bisulfate daily for a minimum of 6 months following the procedure. Ticlopidine at a dose standard with hospital practice may be substituted for clopidogrel, as required by hospital practice or if the patient develops hypersensitivity to clopidogrel.

It is also recommended that all patients should receive  $\geq 75$  mg of aspirin daily for a minimum of 5 years following the index procedure.

Start of these treatments will be documented in the eCRF as well as any changes to and termination of treatment.

#### **7.4.3.2 Randomized Sub-study**

Patients enrolled in the randomized sub-study will be maintained on 75 mg of clopidogrel bisulfate daily for a minimum of 6 months following the procedure. Ticlopidine at a dose standard with hospital practice may be substituted for clopidogrel, as required by hospital practice or if the patient develops hypersensitivity to clopidogrel.

All patients will receive  $\geq 75$  mg of aspirin daily for a minimum of five years following the procedure.

Start of these treatments will be documented in the eCRF as well as any changes to and termination of treatment.

## 8 ASSESSMENT OF SAFETY and PERFORMANCE

Safety and performance will be evaluated at several time points throughout the clinical evaluation. See Appendix IV, Clinical Investigation Flow and Appendix V, Schedule of Events.

### *8.1 Clinical Follow-up for All Patients*

Clinical follow-up will be performed periodically at the following intervals for all patients:

30 days  $\pm$  7 days follow-up telephone contact/office visit

240 days  $\pm$  14 days follow-up telephone contact/office visit

1 year  $\pm$  28 days follow-up telephone contact/office visit

2 year  $\pm$  28 days follow-up telephone contact/office visit

3 year  $\pm$  28 days follow-up telephone contact/office visit

4 year  $\pm$  28 days follow-up telephone contact/office visit

5 year  $\pm$  28 days follow-up telephone contact/office visit

The following information will be collected at each of the time points:

Assessment of anginal status

Data regarding adverse events\*, including related laboratory tests, medications and/or ECGs

\* Following the 2 year follow-up, it is mandatory only to report and collect information on serious adverse events, cardiac adverse events and device related events.

Details of any subsequent repeat coronary angiography and results of such, if applicable

Details of any subsequent coronary interventions (e.g., repeat PCI or CABG)\*\*

Use and compliance of medications to clinical investigation plan (Aspirin and Clopidogrel)

Use and changes in chronic concomitant medications

\*\*All TLR in the Single Arm Study will be clinically indicated.

#### **8.1.1 Additional Follow-up Visits for All Patients**

Additional patient visits may occur as clinically warranted. The following information will be collected:

Assessment of anginal status

Details of any subsequent coronary interventions (e.g., repeat PCI or CABG)\*

Use and compliance to Clinical Investigational Plan medications (Aspirin and clopidogrel)

Use and changes in chronic concomitant medications (Refer to Appendix II for Definition).

\*All TLR in the Single Arm Study will be clinically indicated.

All efforts must be made to obtain follow-up information on patients who have visited, undergone procedures or have been treated for adverse events in a non-study-related hospital(s).

## 8.2 Angiographic Follow-Up for Randomized Sub-study

In addition to the above follow-up visits, imaging (angiography) follow-up will be performed at the following interval on the approximately 450 patients enrolled in the randomized sub-study:

270 days (9 months)  $\pm$  14 days

Information will be collected in accordance with the Angiographic Core Laboratory requirements. Images for all target lesions identified at index procedure must be captured during the 9-month follow-up angiography.

\* All revascularization in the Randomized Sub-study should be classified prospectively as clinically indicated or not clinically indicated by the investigator prior to the reintervention.

| Single target lesion at baseline                                                        | Is 9-Month angiographic follow-up required?                                                                                                                   |
|------------------------------------------------------------------------------------------------|----------------------------------------------------------------------------------------------------------------------------------------------------------------------|
| Revascularization on target lesion before 270 days                                             | No (Unless clinically indicated. Films of target lesion need to be made with the correct angulations and following core lab guidelines before the revascularization) |
| Angiography without target lesion revascularization post-index procedure and prior to 120 days | Yes                                                                                                                                                                  |
| Angiography without target lesion revascularization post 120 days and prior to 270 days        | No (Unless clinically indicated. Films of target lesion need to be made with the correct angulations and following core lab guidelines before the revascularization) |
| All patients are to continue their clinical follow-up visits as described per CIP              |                                                                                                                                                                      |

| Multiple target lesions at baseline                                                     | Is 9-Month angiographic follow-up required?                                                                                                                   |
|------------------------------------------------------------------------------------------------|----------------------------------------------------------------------------------------------------------------------------------------------------------------------|
| Revascularization on all target lesions before 270 days                                        | No (Unless clinically indicated. Films of target lesion need to be made with the correct angulations and following core lab guidelines before the revascularization) |
| Revascularization on one target lesion prior to 120 days                                       | Yes (angiography of all target lesions)                                                                                                                              |
| Angiography without target lesion revascularization post-index procedure and prior to 120 days | Yes (angiography of all target lesions)                                                                                                                              |

|                                                                                                                                          |                                                                                                                                                                                                                                       |
|------------------------------------------------------------------------------------------------------------------------------------------|---------------------------------------------------------------------------------------------------------------------------------------------------------------------------------------------------------------------------------------|
| Angiography with or without target lesion revascularization post 120 days and prior to 270 days (images for all target lesions captured) | No (Unless clinically indicated or some target lesions were not captured in previous angiography. Films of target lesion need to be made with the correct angulations and following core lab guidelines before the revascularization) |
| All patients are to continue their clinical follow-up visits as described per CIP                                                        |                                                                                                                                                                                                                                       |

Follow-up angiography must be performed only for patients who have received at least one study stent.

Collection of angiographic data must be according to the Angiographic Core Laboratory guidelines.

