## **4 CLINICAL EVALUATION DESIGN**

The SPIRIT WOMEN Clinical Evaluation is a prospective, open label, single arm, multi-center study evaluating performance of the XIENCE V EECSS in the treatment of female patients with coronary artery lesions, per its Instructions for Use (IFU). Additionally, this study will include a prospective, single-blind, double arm, randomized multi-center sub-study comparing the XIENCE EECSS (XIENCE V EECSS and XIENCE PRIME EECSS) to the CYPHER SELECT™ Plus Sirolimus-eluting Coronary Stent in the treatment of female patients with coronary artery lesions.

- Approximately 1550 patients will be enrolled in the single arm study (SPIRIT WOMEN Single Arm Study).
- Approximately 450 patients will be randomized 2:1 (XIENCE EECSS vs. CYPHER SELECT™ Plus Sirolimus-eluting Coronary Stent) from up to 35 selected sites (randomized sub-study).

The test device used is XIENCE Everolimus Eluting Coronary Stent System (XIENCE V EECSS and XIENCE PRIME EECSS (randomized sub-study only)). The XIENCE V EECSS has received CE mark approval on 30 January 2006 and FDA approval 02 July 2008. The XIENCE PRIME EECSS has received CE mark approval on 23 June 2009.

The control device used in the randomized sub-study is CYPHER SELECT™ Plus Sirolimus-eluting Coronary Stent. In case a subsequent generation of CYPHER SELECT™ Plus Sirolimus-eluting Coronary Stent is released during the course of the study, it may replace the CYPHER SELECT™ Plus Sirolimus-eluting Coronary Stent.

Assessment of anginal status, collection of data regarding adverse events, details of any subsequent coronary interventions, Clinical Investigation Plan (CIP) medications use and changes in concomitant medications will be collected at 30 days, 240 days and 1, 2, 3, 4 and 5 years post-procedure for all patients.

Evaluation of specific female demographics such as menopausal, hysterectomy and oophorectomy status, past and current use of hormonal contraceptives, and use of weak estrogens will occur for all patients.

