#### **Clinically-indicated Target Lesion Revascularization (CI-TLR):**

In the patient cohorts assigned to clinical follow-up only (such as the SPIRIT WOMEN Single Arm Study), all revascularizations are considered clinically indicated.

A revascularization is clinically indicated if angiography at follow-up shows a percent diameter stenosis  $\geq 50\%$  (QCA assessment) **and** if one of the following occurs:

1. A positive history of recurrent angina pectoris presumably related to the target vessel.
2. Objective signs of ischemia at rest (ECG changes) or during exercise test (or equivalent) presumably related to the target vessel.

3. Abnormal results of any invasive functional diagnostic test (e.g. Doppler flow velocity reserve, fractional flow reserve). The results of the test must be documented in the Case Report Form.

A TLR with a diameter stenosis  $\geq 70\%$  (QCA) in the absence of the above mentioned ischemic signs or symptoms is also considered clinically indicated.

Comment: clinically indicated is a documented, provisional decision to re-intervene based on clinical symptoms and/or results of non invasive functional testing, before any coronary imaging. These criteria are intended to determine clinical indications for reintervention in patients undergoing routine angiographic follow-up. In the patient cohorts assigned to clinical follow-up only, or in studies without routine angiographic follow-up, all revascularizations are considered clinically indicated.

**Not Clinically indicated** TLRs are reinterventions for:

1. all stenoses  $< 50\%$  in the presence or absence of ischemic signs or symptoms;
2. all stenoses  $\geq 50\%$  but  $< 70\%$  without ischemic signs or symptoms.

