#### **Coronary Artery Bypass Graft Surgery (CABG)**

- Acute CABG is defined as immediate transfer from the cath lab to the operative room for emergent bypass surgery during the initial treatment phase.
- CABG during follow-up is only considered as a Clinical-indicated Target Lesion Revascularization if coronary angiography indicates a diameter of stenosis  $\geq 50\%$  of the stented coronary segment associated with one of the following conditions:
  1. A positive history of recurrent angina pectoris presumably related to the target vessel.
  2. Objective signs of ischemia at rest (ECG changes) or during exercise test (or equivalent) presumably related to the target vessel.
  3. Abnormal results of any invasive functional diagnostic test (e.g. Doppler flow velocity reserve, fractional flow reserve). The results of the test must be documented in the Case Report Form.

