**Revascularization:**

Revascularization is defined by the Academic Research Consortium^28 as follows:

- **Target Lesion Revascularization (TLR)**

Target lesion revascularization is defined as any repeat percutaneous intervention of the target lesion or bypass surgery of the target vessel performed for restenosis or other complication of the target lesion. All target lesion revascularizations should be classified prospectively as clinically indicated\* or not clinically indicated by the investigator prior to repeat angiography. An independent angiographic core laboratory should verify that the severity of percent diameter stenosis meets requirements for clinical indication and will overrule in cases where investigator reports are not in agreement. The target lesion is defined as the treated segment from 5 mm proximal to the stent and to 5 mm distal to the stent.

- **Target Vessel Revascularization (TVR)**

Target vessel revascularization is defined as any repeat percutaneous intervention or surgical bypass of any segment of the target vessel. The target vessel is defined as the entire major coronary vessel proximal and distal to the target lesion, which includes upstream and downstream branches and the target lesion itself.

- **Non Target Lesion Revascularization (non-TLR)**

Any revascularization in a lesion other than the target lesion is considered a non target lesion revascularization.

- **Non Target Vessel Revascularization (non-TVR)**

Any revascularization in a vessel other than the target vessel is considered a non-target vessel revascularization.

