**\*Clinically indicated revascularization**

A revascularization is considered clinically indicated if angiography at follow-up shows a percent diameter stenosis  $\geq 50\%$  (core laboratory quantitative coronary angiography assessment) and if one of the following occurs:

- (1) A positive history of recurrent angina pectoris, presumably related to the target vessel;
- (2) Objective signs of ischemia at rest (ECG changes) or during exercise test (or equivalent), presumably related to the target vessel;
- (3) Abnormal results of any invasive functional diagnostic test (eg, Doppler flow velocity reserve, fractional flow reserve);
- (4) A TLR or TVR with a diameter stenosis  $\geq 70\%$  even in the absence of the above-mentioned ischemic signs or symptoms.

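### Section 8.2 permits the investigator to classify a sub-study revascularization after the film is seen, while Appendix II puts this before imaging; separately, the CABG paragraph conflicts with the CI-TLR definition.

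*Protocol*

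**What the plan says.** **Timing.** Protocol section 8.2, the follow-up instruction for the randomized sub-study, wants each revascularization "classified prospectively as clinically indicated or not clinically indicated by the investigator prior to the reintervention". The tables in the same section put imaging ahead of treatment: "Films of target lesion need to be made with the correct angulations and following core lab guidelines before the revascularization". Appendix II gives two other time points. Its TLR definition (under Revascularization) has the event labelled clinically indicated "or not clinically indicated by the investigator prior to repeat angiography". The comment under CI-TLR describes a documented, provisional decision "based on clinical symptoms and/or results of non invasive functional testing, before any coronary imaging", and says that its criteria are meant for patients with routine angiographic follow-up.

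**CABG.** Appendix II counts target-vessel bypass for a target-lesion problem as a TLR. Its CABG paragraph states "CABG during follow-up is only considered as a Clinical-indicated Target Lesion Revascularization if coronary angiography indicates a diameter of stenosis" of at least 50%, together with one of three ischemia conditions. The CI-TLR definition adds a second route: a TLR at 70% or more "in the absence of the above mentioned ischemic signs or symptoms is also considered clinically indicated". The general definition of a clinically indicated revascularization agrees, accepting that degree of stenosis "even in the absence of the above-mentioned ischemic signs or symptoms". For the Single Arm Study, sections 8.1 and 8.6.1 and the CI-TLR definition treat all TLRs or all revascularizations as clinically indicated. The CABG paragraph makes no such exception.

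**Safeguards.** Under Appendix II, the core laboratory checks percent diameter stenosis and can overrule the investigator. Under section 8.6.1, the CEC decides clinical indication in the sub-study from the core laboratory's QCA and the clinical information.

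**The concern.** The point of a prospective label is that the reason to re-treat is on record before the angiogram can influence it. That matters most where every patient has a scheduled film, because a narrowing can then be found and treated in a patient who did not present with symptoms. Section 8.2 is the text that sites follow for that film, and it carries the looser rule.

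The CABG conflict is of a different kind. Section 8.6.1 tells the CEC to adjudicate by the Appendix II definitions, and for one type of event those definitions give two answers.

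At stake is the classification of events in the adjudicated secondary composite of cardiac death, target-vessel MI and CI-TLR (section 5.2). Neither problem can be left to a later analysis document: one is a site instruction and the other an adjudication rule, and both act when the data are recorded.

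**Working it through.** No sample size, power or alpha figure is involved, so the check is a comparison of texts, with the rules applied to the same hypothetical cases.

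**1. Timing**

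| Source | Applies to | Latest point for the investigator's classification |
|---|---|---|
| Section 8.2 | all sub-study revascularizations | before the reintervention |
| Appendix II, TLR definition | TLR | before repeat angiography |
| Appendix II, CI-TLR comment | CI-TLR, provisional decision | before any coronary imaging |

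Take a label entered after the 270-day film but before the repeat PCI. It meets section 8.2 and fails both Appendix II texts. A label entered before the film meets all three. Section 8.2 is therefore looser than Appendix II. It allows the late label but does not call for it.

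**2. Where a late label could matter**

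- Below 50% stenosis: not clinically indicated, whatever the symptoms.
- 70% or more: clinically indicated, whatever the symptoms.
- 50% to below 70%: the label turns on ischemic signs, symptoms or a functional test. The core laboratory's check covers stenosis only, so here the CEC depends on the recorded clinical information.

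**3. Which readouts a routine film can reach**

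- 240-day contact: 240 ± 14 = days 226 to 254.
- Routine film: 270 ± 14 = days 256 to 284.
- Interval from scheduled angina record to film: 256 − 254 = 2 days at least, 284 − 226 = 58 days at most.

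A decision prompted by the routine film falls on day 256 or later. It cannot enter the 30-day or 240-day composite, nor clinical procedure success, which closes at discharge or day seven at the latest. The composite at 1, 2, 3, 4 and 5 years remains exposed.

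**4. CABG rules applied to the same events**

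| Bypass of the target vessel for the target lesion | CI-TLR and general definitions | CABG paragraph |
|---|---|---|
| Sub-study, 75% stenosis, no ischemia | CI-TLR | not CI-TLR |
| Sub-study, 60%, recurrent angina | CI-TLR | CI-TLR |
| Sub-study, 60%, no ischemia | not CI-TLR | not CI-TLR |
| Single Arm Study, no listed ischemia condition | CI-TLR | not CI-TLR |

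The texts disagree in the first and last rows.

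**5. Endpoints that do not use the label.** The primary endpoint (section 5.1) counts any TVR. In-stent late loss, on which sub-study success rests (section 9.4), is a measurement by QCA.

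**The case against.** The best defence is that the timing rules are nested rather than incompatible: a site that follows Appendix II also satisfies section 8.2. Their scope differs too, since 8.2 covers all revascularizations and the Appendix II sentence covers TLR. The label is not the endpoint either, because the CEC decides and the core laboratory can overrule on stenosis. Angina status is also scheduled at 240 days, always before the routine film. For Single Arm bypass, the cohort-specific rule would sensibly prevail over a generic paragraph.

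Much of this stands and limits the reach of the point, but it does not remove it. A site following only section 8.2 can comply and still breach Appendix II. The 240-day record can be up to 58 days old at the film, so it does not replace a classification made just before it. For Single Arm bypass, the word limiting CI-TLR to the listed conditions still needs an exception in the text. In the sub-study, no reading reconciles the CABG paragraph with the route at 70% or more.

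A reader might infer more than the text supports:

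- That 8.2 directs classification after the film. It only permits it.
- That the classifying investigator is unblinded. The sub-study is described as a "prospective, single-blind, double arm, randomized multi-center sub-study" without naming the blinded party. The operator implants the assigned stent, so knowledge of the arm is plausible, but the Protocol does not say that the same person makes the follow-up classification.
- That the CI-TLR rate in an arm could move by 2 to 4 percentage points. That needs an assumed 2% to 4% of patients re-treated at 50% to below 70% stenosis (0.02 to 0.04 × 300 = 6 to 12, and × 150 = 3 to 6), with every label changed and none corrected by the CEC. The Protocol gives no such share, and a distortion between arms would further require the changes to differ by arm.

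**Conclusion.** Both contradictions are in the current text and should be reconciled. Section 8.2 permits a classification that Appendix II rules out, and the CABG paragraph denies CI-TLR status to a bypass that the CI-TLR and general definitions grant.

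The exposure is confined to the CI-TLR secondary composite. For timing, it is mainly sub-study lesions of 50% to below 70% stenosis, at 1 year and later. For CABG, it is bypass for a lesion of 70% or more without ischemia, plus Single Arm bypass if the CABG paragraph is read literally. The primary endpoint and late loss are unaffected, and the timing issue does not reach clinical procedure success. Section 9.4 makes the analysis of this composite descriptive, and the CEC has the final word.

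No numerical shift can be derived from the documents, and none is claimed. The timing conclusion assumes that sites work from section 8.2 and that the CEC has little beyond the site's record on symptoms. The CABG conclusion needs no assumption beyond the wording. This is a correction worth making, not a threat to the trial's main results.

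**What to change.** 1. **Section 8.2 and Appendix II (TLR definition and CI-TLR comment).** Set one time point and separate the two steps. The investigator's provisional classification, based on symptoms and non-invasive tests, is recorded in the eCRF with date and time before any repeat angiogram, including the 270-day film. The criteria that need QCA or an invasive functional test are applied afterwards by the core laboratory and the CEC. The separation is necessary because the 50% and 70% thresholds cannot be assessed before imaging. State whether the rule covers TLR only or all revascularizations.
2. **Appendix II, CABG paragraph.** Replace the free-standing criteria with a reference to the CI-TLR definition, including its provision for stenosis of 70% or more and its Single Arm provision.

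The cost is a short amendment and a brief pre-film eCRF entry. Nobody knows in advance who will be re-treated, so the entry is needed for each sub-study patient having follow-up angiography, at most about 450. No procedure is added and no treatment changes; only the recording and classification of endpoint events are affected.
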